### Adherence

Assessment of adherence to the study will be assessed using the diary that participants and parents complete about their time spent practicing TM or undertaking sitting activities. Also, the TM teacher will reinforce adherence to TM during check-up and practice review sessions.

### Monitoring of Adverse Events

TM is a safe self-management strategy that has been used by many adults around the world, with rarely reported adverse events. These events occurred in individuals with severe psychiatric conditions, but participants with such conditions will be excluded from this study. TM practice can rarely cause mild headaches at the beginning if it is not done correctly. Teachers of the TM technique are trained to correct any difficulties with practice. Any adverse events noted will be reported to the ethics committee and documented.

### Data Management and Statistical Analysis

Data collected during this study will be both hard copy (questionnaires and case report forms) and electronic (excel spreadsheets with participant’s data) files. Hard copy data will be stored securely in the Department of Endocrinology and Diabetes at the Women’s and Children’s Hospital, and electronic data will be stored securely using password protected files. Documents will be retained for 30 years after study completion per current guidelines for data storage.

All data will be analyzed in the deidentified form. Statistical analysis will be performed using the intention-to-treat principle by LG, who will be blinded to the randomization status. A linear mixed-effects model will be used to compare the change in primary outcomes (QOL, specific QOL questionnaire for PCOS, and DASS questionnaires) and secondary outcomes (salivary cortisol levels and blood pressure) between the TM group and control group over the study period. The models will include a random effect for participants to account for the correlation between serial measurements within individual participants. Unadjusted and adjusted analyses will be conducted, with adjustment for important prespecified baseline covariates, including age and BMI (except for the analyses where BMI is the outcome).

While no studies have looked at the effect of TM on QOL in adolescent girls with PCOS, a change in QOL of 21.2 (SD 21.5) will be interpreted as clinically meaningful, as per our previous study in obese adolescents [45]. The sample size was calculated based on a change in QOL of 21.2 (SD 21.5) from baseline to 8 weeks in the TM group, compared to no change in the control group. Therefore, we would require 40 adolescent girls (20 in each treatment group) to have 80% power to detect a difference in the primary outcome of QOL between the TM group and control group (assuming alpha=0.05, and a two-sided statistical test), allowing for 10% attrition based on rates in previous studies that included adolescents in our center [46]. The sensitivity of the effect estimates to missing values will be evaluated using multiple imputation. Analyses will be conducted according to a pre-specified analysis plan using Stata version 15.1 (StataCorp, College Station, Texas, United States).

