### Outcome Measures

Table 3 shows the primary and secondary outcomes that will be measured at baseline (preintervention) and eight weeks (postintervention) at the Women’s and Children’s Hospital.

**Table 3 table3:** Primary and secondary outcome measures.

Outcome measure			Baseline	Eight weeks

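### The planned change comparison names age and BMI as covariates but not the baseline score, so on its natural reading the adjustment does almost nothing and precision is left unused

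*Protocol article*

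**What the plan says.** All of the following is in the Protocol article.

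- **Model** (Data Management and Statistical Analysis): "A linear mixed-effects model will be used to compare the change in primary outcomes" and the named secondary outcomes between groups. "The models will include a random effect for participants to account for the correlation between serial measurements within individual participants".
- **Covariates** (same section): two versions of each comparison are planned. The wording is "Unadjusted and adjusted analyses will be conducted, with adjustment for important prespecified baseline covariates, including age and BMI". The baseline value of the outcome is not named. The list is worded as open, the fixed effects are not written out, and a separate prespecified analysis plan is cited but not shown.
- **Timing** (Outcome Measures): outcomes are "measured at baseline (preintervention) and eight weeks (postintervention". Salivary cortisol differs, with three samples over a day at each of the two assessments (Secondary Outcomes).
- **Sample size** (Data Management and Statistical Analysis): "The sample size was calculated based on a change in QOL of 21.2 (SD 21.5) from baseline to 8 weeks in the TM group". Control girls are assumed to stay level. The calculation uses 80% power, two-sided alpha 0.05, 20 girls per arm and a 10% attrition allowance.

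**The concern.** With only two visits, a participant random effect has a purpose for the questionnaires and blood pressure only if the baseline value is itself an outcome row. The treatment effect is then the group-by-time term, which with complete data is the difference between arms in mean change. Anything constant within a girl drops out of her change, so age and baseline BMI as main effects drop out too.

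Two things follow. Close agreement between the unadjusted and adjusted results would look like robustness, although the algebra largely forces it. And the covariate likely to predict the week-8 score best, the baseline score, is collected on every girl but used only by subtraction. Subtraction is less efficient than regression adjustment and leaves chance baseline differences to act on the result through regression to the mean. With about 20 girls per arm, such differences will not be rare.

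**Working it through.** **1. The plan's own figure.** Inputs from the sample-size paragraph: difference in change 21.2, SD of change 21.5, two-sided alpha 0.05, power 80%, attrition 10%. By the two-sample t-test (noncentral t), 17 per arm gives 79.6% and 18 gives 82.0%, so 18 completers are needed. Then 18/0.9 = 20 per arm, 40 in total. The stated number reproduces exactly, as a change-score design.

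**2. Why age and BMI cancel.** Write girl i's scores as y(i0) = a(i) + b·x(i) + e(i0) and y(i1) = a(i) + b·x(i) + time effect + group effect + e(i1), where x is age or baseline BMI. In y(i1) − y(i0), both a(i) and b·x(i) vanish. With complete two-visit data, the group-by-time estimate from a random-intercept model with free baseline means is the difference in mean change, whether or not x is in the model.

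**3. Check by simulation.** REML fits, 40 girls, r = 0.5, age and BMI both prognostic for the level of the score:

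- *Complete data, 20 data sets.* Adding age and BMI main effects moved the estimate by less than 1e-12 and its SE by at most 0.0001 (mean SE 6.57 in both).
- *4 of 40 week-8 scores missing (10%), 60 data sets.* The estimate moved by 0.44 points on average and by at most 2.2. Mean SE went from 7.02 to 7.01.
- *Complete data, baseline means constrained equal.* Mean SE fell to 5.78, and to 5.61 with age and BMI, which now moved the estimate by 1.07 points on average.
- *Complete data, free baseline means plus covariate-by-time terms.* The estimate moved by 0.86 points on average. Mean SE was 6.73, so these terms alone gave no precision in this set-up, where age and BMI did not predict change.

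**4. Size of the precision loss.** Assume equal score variance s² at both visits and correlation r. The variance of change is 2s²(1−r). The residual variance after regression on baseline is s²(1−r²). The ratio is (1+r)/2. The article gives no r, so a range is shown. Power uses 18 completers per arm, noncentrality 21.2/(SD·√(2/18)), and 33 error degrees of freedom for the baseline-adjusted rows (34 for change). The detectable difference at 80% power is by normal approximation, 2.8016·SD·√(2/18).

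| Analysis | Variance ratio | SD used | Power at 21.2 | Detectable difference |
|---|---|---|---|---|
| Change score | 1 | 21.5 | 82.0% | 20.1 |
| Adjusted, r=0.3 | 0.65 | 17.33 | 94.5% | 16.2 |
| Adjusted, r=0.5 | 0.75 | 18.62 | 91.2% | 17.4 |
| Adjusted, r=0.7 | 0.85 | 19.82 | 87.6% | 18.5 |
| Adjusted, r=0.9 | 0.95 | 20.96 | 83.8% | 19.6 |

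**5. Chance imbalance.** With 20 per arm, the SE of the baseline difference is √(2/20) = 0.32 score SDs, and a gap at least that large arises in about one trial in three. If r = 0.5, an SD of change of 21.5 implies s = 21.5/√(2·0.5) = 21.5, so the gap is about 6.8 points. The change contrast then shifts by (1−r)·6.8 = 3.4 points, which is 3.4/21.2 = 16% of the design effect. Adjusting for the baseline score removes this expected shift. Age and BMI main effects do not.

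**The case against.** The strongest reply is that the article never states the model on which the cancellation depends. It does not say whether baseline means are free or constrained, or whether age and BMI enter with time interactions. A constrained-baseline mixed model would fit its wording, the covariate list is open, and an analysis plan exists that is not shown. A condensed article may leave such detail to that plan. This stands as a limit: the article supports saying that the baseline score is not named, not that it is excluded. It does not remove the point, because nothing stated shows that the baseline score is used beyond forming the change, and the sample size rests on change as well.

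A reader might also infer that the adjusted analysis is bound to be identical and checks nothing. That holds only for complete data and main effects. At the planned attrition the two analyses differ somewhat, through girls without a week-8 score.

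Nor does the two-value argument carry over to cortisol. With three samples per assessment, a participant random effect has a clear purpose there.

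Finally, the size depends on r. At r = 0.8 to 0.9 the variance saving is only 10% to 5%.

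**Conclusion.** The point holds as an efficiency improvement, not as an error. On the natural reading, the two named covariates contribute almost nothing to the treatment contrast for the questionnaires and blood pressure, and the baseline score goes unused as a covariate. The variance saving from using it is 35% at r = 0.3, 25% at 0.5, 15% at 0.7 and 5% at 0.9. It is positive for every r below 1, given equal variances at the two visits and apart from one lost degree of freedom.

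A reader might infer that the planned analysis is biased or the trial underpowered. The documents support neither. Under randomisation the change contrast is unbiased, and 18 completers per arm meet the stated 80% power on change. The imbalance in step 5 is a shift given the baseline gap that happens to occur, and it averages to zero over randomisations. Nor is it a fault that the article does not say which of the unadjusted and adjusted analyses is primary, since the analysis plan may settle that.

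**What to change.** Before unblinding, write out the fixed effects for the questionnaire outcomes and blood pressure in one of two forms:

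- ANCOVA of the week-8 score on group, baseline score, age and baseline BMI, with t-based inference; or
- the mixed model with baseline means constrained equal across arms, plus age-by-time and BMI-by-time terms. This form also keeps girls who have only a baseline score.

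For cortisol, apply the same principle with the three daily samples modelled explicitly. The unadjusted change comparison can stay as a supporting result.

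The cost is a sentence or two in the analysis plan and, for ANCOVA, a few error degrees of freedom. No new data, visits or participants are needed, and the sample size can stay as it is.

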## Results

Recruitment started in May 2019 and is expected to be completed by June 2020. It is expected that adolescent girls with PCOS practicing TM over eight weeks will have a significant improvement in QOL and psychological distress compared to adolescents in the control group. Also, it is expected that adolescent girls in the TM group will have lower salivary cortisol levels and lower blood pressure. The results from this trial are anticipated to be published by September 2020.

## Discussion

PCOS is the most common endocrine condition affecting women of reproductive age and is associated with many comorbidities, which contribute to impaired QOL and increased psychological distress [3,5,7,8]. Currently, health care professionals have limited strategies to offer to improve the well-being of this population beyond hormonal and metabolic treatments. Evaluating the efficacy of a novel sustainable strategy in the management of PCOS will assist in the overall management of this condition from adolescence and into young adulthood, as once this strategy is learned, it can be practiced for life. Although studies are suggesting that mindfulness may have a role in improving QOL in women with PCOS, there are no studies conducted in adolescents and no studies of TM in women or adolescents with PCOS.

To our knowledge, this is the first study evaluating the effect of TM on QOL and psychological distress in adolescent girls with PCOS. The current study will evaluate a simple, translatable strategy to improve QOL and well-being in adolescent girls with PCOS. TM will be easy to implement in the long term, with no additional costs once the strategy has been learned. This intervention can also be potentially taught in schools as part of classroom activities.

## Abbreviations

BMI: Body mass index
DASS: Depression, Anxiety and Stress Scale
PCOS: Polycystic ovary syndrome
QOL: Quality of life
TM: Transcendental Meditation
